### Sample Size

The target sample size was determined based on a retrospective analysis conducted at 5 participating institutions. This analysis reviewed the number of cases of CDB and the rate of rebleeding within 30 days over a 1-year period (January-December 2019; UMIN000049020). Among the patients who did not undergo endoscopic hemostasis for CDB, the 30-day rebleeding rate was 1 of 11 (9.1%) patients who received orengedokuto, compared with 15 of 48 (31.3%) patients who received only conservative treatment (*P*=.23).

The sample size was calculated based on the primary end point: the proportion of patients with rebleeding. Assuming a rebleeding rate of 31.3% in the placebo group (standard treatment only) and 9.1% in the orengedokuto treatment group, the minimum number of patients required to achieve a 2-sided significance level of 5% and a power of at least 80% was estimated. Using the Fisher exact test for a 2-sample comparison of proportions, with the PROC POWER procedure in the statistical analysis system, the required sample size was calculated to be 57 patients per group. Considering potential dropouts and ineligible cases, the planned total enrollment is set at 120 patients.

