### Statistical Methods

The full analysis set (FAS) will include all enrolled participants, excluding those who are found to be ineligible, those who do not receive any study treatment after enrollment, and those for whom no postenrollment measurements are available. The per-protocol set will include participants in the FAS, excluding those for whom the primary outcome is not evaluable and those with major protocol deviations, such as incorrect treatment allocation, use of prohibited concomitant treatments, or treatment adherence of 70% or less. The safety analysis set will include all enrolled participants who receive at least one dose of the study treatment.

For the primary end point, the FAS will be used as the analysis population. The proportion of patients with rebleeding will be calculated for each group, and intergroup comparisons will be performed using Fisher exact test, consistent with the method used for sample size calculation. A 2-sided significance level of 5% will be applied. Additionally, a sensitivity analysis will be conducted using the per-protocol set to assess the robustness of the results.

For the secondary end points, the FAS will also be used as the analysis population. Statistical comparisons will be performed between the 2 groups for the following variables:

Mean duration of hospitalization;Mean number of days until the initiation of oral intake;Severity of rebleeding (including timing and degree of anemia); andProportion of patients with recurrent rebleeding (re-rebleeding)

The Wilcoxon rank-sum test will be used to analyze continuous variables. Fisher exact test will be used to analyze categorical variables. No adjustment for multiplicity will be made for the secondary end point analyses, which will be considered exploratory. Further details will be prespecified in the statistical analysis plan, which will be finalized before database lock and unblinding.

The safety analysis set will be used for the safety analysis. Safety will be evaluated separately for the treatment and follow-up periods. Adverse events will be assessed in terms of type, frequency, severity, and causal relationship with the investigational drug. The incidence rates of adverse events will be calculated and compared between groups. If statistical testing is applied, the Fisher exact test will be used for comparison.

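### Timing and degree of anemia of a rebleed exist only for patients who rebleed, so the planned rank-sum comparison in the full analysis set would compare about 18 placebo with 5 orengedokuto patients, a subset not protected by randomisation if the drug works

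*Protocol article*

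**What the plan says.** Under Statistical Methods, the protocol article sets the population for this family of analyses: "For the secondary end points, the FAS will also be used as the analysis population". The list of variables to be compared between the two groups includes "Severity of rebleeding (including timing and degree of anemia". Two tests are named for the whole list: "The Wilcoxon rank-sum test will be used to analyze continuous variables", and Fisher's exact test for categorical variables. The same section says that missing values stay missing and are not imputed. It calls the secondary analyses exploratory and leaves further detail to a statistical analysis plan that is to be final before database lock and unblinding.

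The list also has "Mean duration of hospitalization" and, likewise as a mean, the days until oral intake starts.

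**The concern.** The time of a rebleed and the anemia it causes are undefined for a patient who never rebleeds. These values are not missing in the usual sense. They do not exist, and the article does not say how such patients enter the comparison. Neither named test handles censoring. If nothing is added, only rebleeders can contribute.

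Whether a patient rebleeds is decided after randomisation and is what the drug is meant to change. If the drug works, the two sets of rebleeders are different kinds of patients. A difference in timing or anemia between them could then reflect which bleeds were prevented and not any effect on the bleeds that remain. These results would also inform the larger confirmatory study that the Discussion foresees.

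**Working it through.** **1. The plan's own figure.** Inputs from Sample Size: "Assuming a rebleeding rate of 31.3% in the placebo group (standard treatment only) and 9.1% in the orengedokuto treatment group"; two-sided 5% level; power of at least 80%; Fisher's exact test; and "the required sample size was calculated to be 57 patients per group". Exact enumeration of Fisher power gives 79.3% at 56 per group and 80.3% at 57. An arcsine approximation gives 79.3% and 80.1%. The figure of 57 reproduces.

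**2. Expected rebleeders** (n × planning rate).
- Placebo: 57 × 0.313 = 17.8.
- Orengedokuto: 57 × 0.091 = 5.2.
- Together: 23.0 of 114 = 20.2%, so 79.8% of the FAS has no rebleed to time or grade.
- At 60 per group (120 enrolled): 18.8 and 5.5, or 24.2 of 120 = 20.2%.
- Binomial 95% ranges at 57 per group: 11 to 25 (placebo) and 1 to 10 (orengedokuto). The chance of 3 or fewer orengedokuto rebleeders is 23%.

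**3. Power of the rebleeders-only test.** Simulated rank-sum test, 18 against 5, normal shift, exact two-sided p at 5%. Separate runs agree to within about two percentage points.

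| Shift | Power |
|---|---|
| 0.5 SD | about 13% |
| 0.8 SD | about 28% |
| 1.0 SD | about 42% |
| 1.5 SD | about 75% |

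**4. How far selection could go.** The planning rates imply that the drug prevents 1 − 0.091/0.313 = 70.9% of rebleeds. Take the extreme assumption that these are exactly the mildest 70.9% on a normal severity scale among rebleeders. The mean of a standard normal above its 70.9th percentile (z ≈ 0.55) is 0.343/0.291 = 1.18 SD. The remaining bleeds would look about 1.2 SD worse although none was made worse.

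A simulation with the same pattern, taking rebleeders as the upper tail of a severity scale in all patients, gives a difference of 0.67 on that scale. Placebo rebleeders have an SD of 0.52 there, so this is 0.67/0.52 ≈ 1.3 of their SDs. The rebleeders-only test is significant in about 70% of such trials, against the drug. Ranking the whole FAS with no rebleeding as best favours the drug significantly in about 78%. If the drug mainly prevented severe bleeds, the bias would reverse.

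**5. No drug effect.** With 31.3% in both arms, about 18 rebleeders per arm are expected (57 × 0.313 = 17.8). They remain comparable.

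**6. What a whole-FAS severity rank measures.** At 57 per group and the planning rates, with identical severity among rebleeders in both arms, the ranking is significant in about 84% to 85% of simulated trials. Fisher's test on the primary end point is significant in about 80%, and the two verdicts agree in about 95%. The rank is largely the primary end point again.

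**7. Stratifying a log-rank test.** The four allocation factors with at least 6 sites give 6 × 2 × 2 × 2 = 48 or more strata for about 23 events, which is impractical.

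**The case against.** The strongest reply is that the error is inferred. The article never says that the comparison is limited to rebleeders and does not assign a test to severity by name. A severity grade could be categorical. A rank-sum test in the FAS is also how one would test a whole-FAS ranking with non-rebleeders in the best position. On that view only a scoring rule is absent, and the analysis plan can supply it. This stands in part for degree of anemia. It fails for timing: the natural whole-FAS analysis needs censoring, and the article names no method that allows it.

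Three further objections stand. A whole-FAS severity rank has its own problem of interpretation (step 6). A hemoglobin value is not assured for every rebleed: Interventions schedules blood tests before enrollment, on the day after the intervention and on day 15, day 31 may be a telephone contact, and visible blood alone can satisfy the primary definition. Finally, the secondary analyses are labelled exploratory. That label deals with multiplicity and not with selection, but it does limit the weight of the point.

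A reader might infer that an effective drug will look harmful on severity. The documents do not support this. The 1.2 SD figure needs an extreme pattern of prevention, and nothing in the article indicates which bleeds the drug would prevent. Nor is the comparison without any power, since 1.5 SD would be detected about 75% of the time.

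**Conclusion.** The point holds, resting mainly on timing. As written, the population and the rank-sum test do not fit a variable that about 80% of the FAS cannot have. The expected comparison is about 18 against 5 patients, with power of about 13% to 42% for shifts of 0.5 to 1.0 SD. To the extent that the drug works, the comparison is not randomised, and its bias is unknown in size and direction.

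This rests on the planning rates, on 57 evaluable patients per group, and on reading the article as giving no rule for non-rebleeders. Restriction to rebleeders is a consequence of the text and is not stated in it. A reader should not infer that the primary analysis is affected. The weight is moderate: the change is worth making before the analysis plan is final.

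The listing of means beside a rank-sum test is a small wording mismatch. The test does not address a difference in means.

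**What to change.** - **Timing:** analyse time from enrollment to first rebleeding in the whole FAS, with Kaplan-Meier curves and an unstratified log-rank test, censored at day 30 or last contact.
- **Degree of anemia:** report it among rebleeders descriptively, without a between-group test.
- **Optional:** add a whole-FAS ranking with no rebleeding as the best rank. Label it as a composite of occurrence and severity that largely repeats the primary end point, and state a rule for rebleeds without a hemoglobin value.
- **Wording:** drop the word mean for hospital stay and days to oral intake, or report a median or Hodges-Lehmann shift with the rank-sum test.

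The cost is wording in the protocol and analysis plan, plus a check that the case report form records the date of each rebleed. The timing result will overlap with the primary result, and a tested comparison of severity is given up. With 48 of 120 patients enrolled as of June 2026 and the key code closed until the case report forms are final, the change can be made without knowledge of results.

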### Oversight and Monitoring

#### Composition of the Coordinating Center and Trial Steering Committee

The management structure comprises a PI, a trial steering committee, and a data-monitoring committee. The trial steering committee will be responsible for conducting the trial and will meet regularly to discuss trial progress. The team members will include a clinical epidemiologist, a specialist in Kampo medicine, and a statistician.

The data-monitoring committee will review the interim safety data and periodically review the conduct of the study. All data will be monitored monthly. The PI shall appoint a data management supervisor who will be responsible for overseeing and coordinating the timely completion of CRFs, data collection, and the preparation of appropriate datasets. The data management supervisor will monitor the progress of CRF completion and data entry and will be responsible for data review and cleaning. Furthermore, the data management supervisor will be accountable for ensuring the quality of the analysis dataset.

#### Composition of the Data Monitoring Committee, Its Role, and Reporting Structure

The PI will appoint a data management officer to manage and coordinate the creation of CRFs and data collection without delay and the creation of an appropriate dataset. The data management officer will manage the progress of CRF creation and data entry and will be responsible for data review and cleaning. The data management officer will also be responsible for the quality of the dataset used in the analysis.

The PI will appoint a central monitor to confirm whether the study is being conducted safely and in accordance with the research protocol and the Clinical Research Act and whether data are being collected accurately. The monitor will submit the monitoring results to the PI.

#### Adverse Event Reporting and Harms

The PI or subinvestigator shall promptly provide appropriate treatment to the study participant in the event of an adverse event and document the details in the medical records. If necessary, suspension or discontinuation of the study will be considered. If treatment or other medical interventions are required, this will be explained to the participant. The name of the adverse event, its severity, causality, outcome, and other relevant details will be assessed and recorded in the CRF.

An Independent Efficacy and Safety Evaluation Committee will be established for this study. This committee will consist of experts who are independent of the study and will be responsible for assessing its progress, safety data, and key end points. The committee will provide recommendations to the PI regarding whether to continue, suspend, terminate, or revise the study protocol, as necessary.

#### Frequency and Plans for Auditing Trial Conduct

The PI shall report on the implementation status of the specified clinical study to the administrator of the implementing medical institution annually, within 2 months after each 1-year period from the date the study plan was published on the Japan Registry of Clinical Trials. Subsequently, the PI will submit a periodic report to the ethics committee specified in the study protocol.

The items to be reported on the implementation status are as follows:

The number of participants enrolled in the specified clinical study;The occurrence and subsequent course of any diseases or conditions;The occurrence of noncompliance and subsequent responses;Evaluation of safety and scientific validity; andInformation regarding the involvement of pharmaceutical companies or other entities, as stipulated in the conflict-of-interest management standards

When the PI reports to the ethics committee, they shall promptly share the information with the other investigators. The investigators shall then promptly report the content of the information to the administrators of their respective medical institutions.

Auditing trial conduct is not planned but will be conducted as required.

#### Plans for Communicating Important Protocol Amendments to Relevant Parties

The PI will document any significant changes to the protocol and obtain approval from the review committee. Once the changes are approved, a formal notification will be sent to all PIs, co-investigators, etc. If necessary, opportunities for explanation will be established to prevent misunderstandings or lack of understanding. If the changes affect the participants, the informed consent document will be updated and reconsent will be obtained as necessary.

In addition, all change notifications and confirmation documents will be recorded in the document management ledger and maintained in a state that can be viewed during audits and monitoring.

### Secondary Use of Information

Information obtained from research participants during this study may be used for future research projects that have not yet been identified at the time that consent is obtained. In such cases, a new research protocol will be prepared, reviewed by the ethics committee, and implemented only after approval is granted.

### Dissemination Plans

The results of this study will be presented at conferences and published in scientific journals. We will also prepare lay summaries for the public and endeavor to disseminate the results more widely.

## Results

This study received funding from the Japan Agency for Medical Research and Development in May 2025. Enrollment is scheduled from July 2025 to December 2027. As of June 2026, we have enrolled 48 participants. All follow-up and data collection activities will be finalized by February 2028. Results are anticipated to be completed in the first quarter of 2028.

## Discussion

This study aims to determine whether orengedokuto can safely reduce rebleeding in patients with CDB who have achieved spontaneous hemostasis but are not candidates for endoscopic hemostasis because the source of bleeding cannot be identified. If this research hypothesis is confirmed, it will provide the first high-quality evidence supporting oral therapy for the prevention of rebleeding in this patient population, which is clinically challenging to manage.

Endoscopic therapy is recommended in cases of active bleeding or SRH. A multicenter retrospective study involving 5823 cases of CDB reported that both early and late recurrent bleeding rates were significantly lower in patients with definitive CDB who received endoscopic treatment than in those with presumptive CDB who were managed conservatively [25]. Moreover, the study showed that the endoscopic treatment of SRH significantly reduced early recurrent bleeding rates compared with untreated SRH (17.4% vs 26.7%, *P*=.04), highlighting the importance of actively identifying SRH.

However, active bleeding is often not observed during colonoscopy, and the presence of multiple diverticula makes the identification of the bleeding source difficult, resulting in a relatively low detection rate. As a result, despite the risk of rebleeding, many patients are managed with conservative treatment. Currently, there is no evidence supporting the efficacy of pharmacological therapy in achieving hemostasis when endoscopic intervention is not feasible. Consequently, patients often require repeated blood transfusions and frequent endoscopic examinations owing to recurrent bleeding, which not only reduces their quality of life but also imposes a significant economic burden. This study was designed to address this critical lack of evidence.

Orengedokuto (Huanglian Jiedu Tang) is a traditional Kampo medicine. In addition to its well-documented clinical applications in traditional medicine, a growing body of modern research has focused on elucidating the pharmacological mechanisms of orengedokuto at the molecular level. Orengedokuto has been suggested to contribute to primary hemostasis through mechanisms such as vasoconstriction of small vessels and suppression of excessive activation of the coagulation-fibrinolysis system. Several studies have demonstrated its ability to suppress oxidative stress by reducing the formation of reactive oxygen species and enhancing endogenous antioxidant systems [26]. This activity is considered to be one of the fundamental mechanisms underlying its therapeutic effects in managing chronic inflammatory conditions, tissue injury, and metabolic disorders. Furthermore, under the administration of nonsteroidal anti-inflammatory drugs, orengedokuto has been suggested to exert mucosal protective effects by increasing prostaglandin E2 production [27] and elevating adenosine levels by suppressing adenosine deaminase expression [28].

In our retrospective study of patients with CDB who did not undergo endoscopic hemostasis, the rebleeding rate was lower in the orengedokuto group than in the conservative treatment group, although the difference was not statistically significant. Based on these findings, we initiated a double-blind randomized controlled trial to evaluate the efficacy and safety of orengedokuto in preventing rebleeding in patients with CDB of unknown origin. This study has several strengths. To the best of our knowledge, this is the first multicenter, double-blind, randomized, placebo-controlled trial to evaluate the efficacy of Kampo medicine for the prevention of gastrointestinal bleeding. This study specifically targets patients for whom no established preventive therapy currently exists, thereby addressing an unmet clinical need. However, it is important to recognize some limitations. First, the sample size calculation is based on a very small retrospective cohort of just 11 patients in the orengedokuto group. The assumed absolute risk reduction of around 22% could lead to an overestimation of the true treatment effect. Since this is an exploratory study, the sample size is relatively small; if efficacy is demonstrated, the results will need to be confirmed in a larger confirmatory study. Furthermore, because the follow-up period was limited to 30 days, it was not possible to evaluate long-term rebleeding or late adverse events. Future studies with a longer follow-up period are needed to confirm the durability of the treatment effect and to evaluate potential late complications.

If this study demonstrates that the frequency of rebleeding in patients with diverticular bleeding who cannot be treated by colonoscopy can be reduced, patients’ quality of life may improve and medical costs will decrease. Furthermore, our findings may be incorporated into treatment guidelines for diverticular bleeding.
